1. INTRODUCTION

The term high-grade cervical intraepithelial neoplasia (CIN) is used to define lesions previously referred to as moderate dysplasia (CIN II) and severe dysplasia / in-situ carcinoma (CIN III) (1).

Literature reviews regarding the natural history of these lesions indicate that 43% of untreated NIC II lesions will regress in the absence of treatment, while 35% will persist and 22% will progress to in-situ carcinoma or invasive carcinoma (2). In comparison, 32% of NIC III lesions will regress spontaneously, 56% will persist and 14% will progress (1, 3).

The treatment of high-grade CIN (CIN II, III) is divided according to the patient's colposcopic evaluation. In cases of satisfactory colposcopy (visible squamous-columnar junction), both ablative and excisional methods are adequate (4). Ablative methods include cryotherapy, laser vaporization, electrocautery, diathermy, cold coagulation, while excisional methods include LEEP (excisional electrosurgical loop) also called High-Frequency Surgery (CAF), laser conization and cold conization.

It is important to emphasize that excision procedures allow a detailed assessment of all excised tissue, thereby reducing the risk that a micro-invasive lesion or occult invasive carcinoma is inadvertently treated as a pre-invasive lesion. When the colposcopic evaluation is unsatisfactory (squamous-columnar junction not visible) there is a chance of up to 7% of the diagnosis of occult invasive carcinoma in the conization specimen by a biopsy showing NIC II/III. Thus, diagnostic conization procedures that allow pathological examination of the tissue of the endocervical canal are usually used for women with biopsies confirming NIC II/III who have an unsatisfactory colposcopic evaluation.

The complications inherent to conization involve stenosis of the cervical canal, amenorrhea, dysmenorrhea and deep dyspareunia. (5)

1.1. Cervical canal stenosis

Stenosis of the cervical canal is the most important complication due to the clinical repercussions that can vary from menstrual cramps followed by hematometrium, infertility and the impossibility of early detection of recurrence and/or recurrence of the premalignant lesion (5, 6).

Studies show a rate of cervical canal stenosis ranging from 3 to 25% after laser conization and 1.3 to 19% when performed with LEEP (5-10). It can be diagnosed within 28 months of conization. (6)

Studies indicate that the variables of wide excision of the entire endocervix (RR 5.07) and extension of the excision of> 2cm (RR 1.95) are associated with a high risk of cervical stenosis after conization. (6)

Although many studies report cervical stenosis after conization, few studies in the literature describe techniques for treating endocervical canal stenosis. When describing some type of intervention, the study is not randomized and with a small number of patients. Among the techniques described there are reports of the use of devices that maintains the patency of the cervical for a brief period in order to avoid restenosis of the canal and maintain the patient's fertility or follow-up in women of non-fertile ages. (11, 12) (13)

Analysis of studies that used some type of device to prevent cervical stenosis

| Authors | Year | N | Device | Length of stay device | Type of study | Post device stenosis rate | Follow-up /  Complications  (N) |
| --- | --- | --- | --- | --- | --- | --- | --- |
| Nasu k et al | 2010 | 4 | DIU-Nylon | 3 months | Case report | 0 | Does not describe/ 0 (zero) |
| Luesley, DM et al | 1990 | 33 | stent | 2 weeks | Pilot Study | 6% | 6 months /  0 (zero) |
| Dorothee Grund et al | 2007 | 1 | Stent Vascular | 9 months | Case report | 0% | 11 months/  0 (zero) |

Table 1

As there is no indication and consensus procedure in the literature to prevent stenosis of the endocervical canal, this study proposes and uses a new device created at the Barretos Cancer Hospital (HCB), called the Uterine Endocervical Canal Dilatation Device (DUDA) (figure 1) in patients undergoing conization in an attempt to assess and avoid the post-CAF stenosis index.

2. JUSTIFICATION

Currently, there is no standard and consensual standard procedure for the prevention and treatment of cervical canal stenosis after a conization procedure. There is a limited number of clinical trials, all non-randomized, that use temporary devices in an attempt to avoid this type of complication (11, 12). Although the conclusions of these studies are favorable, more robust evidence about the safety and efficacy of these methods is still lacking. It is necessary to explore with greater scientific rigor the application of devices in the cervical canal to prevent its stenosis.

3. OBJECTIVES

3.1. Primary objective:

To evaluate the effectiveness of a new cervical device called DUDA in preventing late cervical canal stenosis in women undergoing conization with a high-frequency scalpel.

3.2. Secondary objectives:

3.2.1. Assess the safety of using the device;

3.2.2. Compare the quality of life in women with and without the device after surgery;

3.2.3. Compare the rate of visualization of the squamous-columnar junction (JEC) in women who used the device or not (3 and 6 months after surgery);

3.2.4. Describe menstrual periods in women who used device placement after surgery.

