3) Asepsis with degerming iodine throughout the perineal and vaginal region. If the patient has an allergy to iodine, asepsis is performed with chlorhexidine gluconate solutions;

4) Placement of sterile surgical drapes;

5) Introduction of the vaginal speculum and identification of the cervix;

6) Passage of acetic acid and Lugol´s iodine in the cervix and vaginal walls to identify positive acetowhite and iodine areas;

7) Local anesthesia with 2% lidocaine with a vasoconstrictor, infusing 2 ml in each quadrant of the cervix (3, 6, 9 and 12h);

8) Passage of the diathermic loop connected to the generating source in “cut” mode (level 60) in a single pass, with or without enlarging the endocervical canal (depending on the indication of each case);

9) Hemostasis with a "ball" electrode connected to the generating source in "coagulation" mode (level 60).

After this surgical procedure, the patient remains in the hospital for a few more hours for recovery from anesthesia and observation of eventual postoperative bleeding. The patient is discharged from the hospital with guidance on the use of analgesics (if necessary) and to abstain from sexual intercourse for at least 30 days due to the risk of bleeding during intercourse.

4.7 Procedure for placing the endocervical device (DUDA):

After the end of the CAF, and with the patient still positioned on the operating table, the surgeon will place the DUDA device on the cervix. Device deployment is quick and requires no more than 5 minutes. It should be noted that this procedure represents the experimental part of the study.

The surgeon will carefully insert the nail into the endocervical canal until the flat circular surface of the device rests on the cervix. By means of the simple suture in four points (2-0 polypropylene thread, atraumatic needle), the device will be fixed to the surface of the cervix. In the event that the residual neck has a very flat surface, the device may be attached to the lateral fornices.

4.8 Criteria for not placing or removing the device:

Even if the participant has signed the Free and Informed Consent Form and the randomization has already been carried out, the DUDA device will not be placed on patients who have any complications during the performance of the CAF and that require additional procedures, such as bed bleeding. surgical procedure requiring hemostatic procedures with suture and/or use of a vaginal tampon.

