4.9.2. Second step: analysis of the effectiveness

The participants in the first stage will not be part of the second. Although the main objective of this step is to evaluate the effectiveness of the device in preventing post-conization cervical canal stenosis, safety and quality of life issues will also be analyzed. The observation period for the second stage will be two years.

In the second stage, 240 participants will be recruited randomly balanced 1: 1 in two groups: one who will receive the DUDA device after CAF and another who will not receive it. Randomization, active search and patient management will take place at the outpatient clinic after the signature of the TLCE by the nurse responsible for clinical research in the department and will be carried out in blocks of 4, through the REDCap program.

4.10. Study outcomes:

4.10.1. Device security:

The safety analysis will be performed up to 30 days after surgery. The definitions of CTCAE (Common Terminology Criteria for Adverse Events) version 4.0 will be adopted as a reference for the security assessment of the device. For that, two main safety events will be considered during its use: vaginal bleeding and uterine infection. Below are the gradations for the two main security events defined by CTCAE version 4.0.

a) Vaginal bleeding:

- Grade 1: mild bleeding, identified on clinical examination or imaging study. No intervention is indicated;
- Grade 2: moderate bleeding; Medical intervention is indicated;
- Grade3: bleeds, intense; need for a blood transfusion; radiological or endoscopic intervention is indicated;
- Grade 4: bleeding determines life-threatening; urgent surgical intervention is indicated;
- Grade 5: death from bleeding.

b) Uterine infection:

- Grade 1: (there is no category for this event);
- Grade 2: moderate symptoms; oral intervention is indicated (eg: antibiotics, antifungal, antiviral);
- Grade 3: intravenous intervention is indicated (eg: antibiotics, antifungal, antiviral); radiological intervention or surgical intervention are indicated;
- Grade 4: infection determines life-threatening; urgent surgical intervention is indicated;
- Grade 5: death from bleeding.

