5. SAMPLE CALCULATION

5.1. First step:

For the safety analysis of the device, 25 women will be included, as advised by the National Ethics and Research Commission (CONEP).

5.2. Second stage:

The sample calculation assumed the premise of a cervical canal stenosis rate of approximately 15% to 20% after the CAF described in the literature and reduced to 6% with the use of an endocervical device according to the uncontrolled trial by Luesley et al (11) Considering this difference in stenosis rates (15-20% vs. 6%), an alpha error of 5%, a beta error of 20% and a balanced allocation 1: 1, the sample estimate ranges from 104 to 203 in each group. Therefore, this stage of the study will recruit 120 women in each arm, totaling 240 participants.

It is estimated that recruitment will take place between 1 to 3 weeks in the first stage and between

25 to 30 weeks in the second stage, since the potential for recruitment is 06 to 10 surgeries per week.

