6. STATISTICAL ANALYSIS

The casuistry will be characterized by means of descriptive statistics. Quantitative variables will be described by means and standard deviation or median and 25-75 percentiles, depending on their distribution. Qualitative variables will be described using absolute and relative frequencies.

The rates of stenosis of the cervical canal will be compared between the groups at different times of observation from the moment 2-PO using the chi-square test or Fisher's exact test, depending on the values ​​observed in the contingency tables. Adverse events are characterized by means of absolute and relative frequencies, and inferences are made using a 95% confidence interval. The calculation of the scores of the domains of the FACT-Cx questionnaire will follow the guidelines of the manual of the organization FACIT (Functional Assessment of Chronic Illness Therapy). The scores will be compared between the groups at each moment of observation using the t-test or Mann-Whitney test, depending on the data distribution. In all statistical calculations, the level of significance considered will be 5%.

An interim analysis is foreseen in the transition from the first to the second stage of the study and when the casuistry of the second stage reaches 25%, 50% and 75% of the recruitment estimate.

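### Objective 3.2.3 groups women by device use, while section 4.8 withholds the device after randomisation; followed as written, the junction-visualisation comparison is not randomised

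*Protocol*

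**What the plan says.** - **Objective.** Protocol 3.2.3 compares the rate of junction visualisation at 3 and 6 months "in women who used the device or not". The neighbouring objective, 3.2.2, reads "Compare the quality of life in women with and without the device after surgery".
- **Withholding rule.** Section 4.8 states: "the DUDA device will not be placed on patients who have any complications during the performance of the CAF". This applies even where consent is signed and "the randomization has already been carried out". The example given is bleeding that needs sutures or a vaginal tampon.
- **Groups.** Section 4.9.2 recruits 240 women, randomised 1:1 into two groups, "one who will receive the DUDA device after CAF and another who will not receive it".
- **Analysis.** For stenosis, section 6 states: "The rates of stenosis of the cervical canal will be compared between the groups". For FACT-Cx it states: "The scores will be compared between the groups at each moment of observation". It describes no comparison for junction visualisation.

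**The concern.** The protocol itself creates women who are randomised to the device but never use it. For stenosis and quality of life, section 6 points to the groups, which section 4.9.2 forms by randomisation. For junction visualisation nothing does so, and the only grouping rule in the document is the wording of 3.2.3, which sorts women by use.

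The rule in 4.8 acts on one arm only. A complicated excision in the device arm takes a woman out of the users. A complicated excision in the control arm changes nothing, since she was never to have the device. As-used groups would therefore have no complicated excisions on one side and those of both arms on the other. They differ by something that happened at surgery, whatever the device does. At stake is whether this secondary comparison keeps the protection of randomisation. Section 2 justifies the trial by the lack of randomised evidence on such devices.

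**Working it through.** The protocol states no figure for this point. The only planned number used is 120 women per arm (section 5.2). The range given there, 104 to 203 per group, is reproduced by a two-sided 5% test with 80% power and continuity correction (20% v 6% gives 104; 15% v 6% gives 203). Nothing below changes it.

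**Assumptions, none of them in the protocol**
- The device has no effect on visibility.
- The same share *w* of excisions is complicated in each arm: 5% or 10%.
- The junction is visible in *v_u* = 80% of uncomplicated cases and *v_c* of complicated cases. *v_c* is varied, with 50% as the main illustration.
- Every woman whose device is withheld is counted as a non-user.

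**Group sizes as used**
- Users: 120(1 − w), none complicated.
- Non-users: 120 + 120w = 120(1 + w), of whom 2 × 120w = 240w are complicated.
- At 5%: users 0 of 114 complicated; non-users 12 of 126 (9.5%).
- At 10%: users 0 of 108 complicated; non-users 24 of 132 (18.2%).

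**Visibility among non-users** = [120(1 − w)·v_u + 240w·v_c] / [120(1 + w)]
- At 5%: (114 × 0.80 + 12 × 0.50)/126 = (91.2 + 6)/126 = 77.1%, against 80.0% in users.
- At 10%: (108 × 0.80 + 24 × 0.50)/132 = (86.4 + 12)/132 = 74.5%, against 80.0% in users.

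**Spurious difference** (users minus non-users) simplifies to [2w/(1 + w)] × (v_u − v_c). The multiplier is 0.0952 at 5% and 0.1818 at 10%.

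| Assumed visibility in complicated cases | 5% complicated | 10% complicated |
| --- | --- | --- |
| 50% | +2.9 points | +5.5 points |
| 70% | +1.0 | +1.8 |
| 80% (equal prognosis) | 0 | 0 |
| 90% | −1.0 | −1.8 |

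In the 50% row, a two-sided 5% test (normal approximation, pooled standard error under the null) would reject in about 8% of trials at 5% complicated and about 17% at 10%, instead of 5%.

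**By randomised arm**, both arms have expected visibility (1 − w)·v_u + w·v_c. At v_c = 50% that is 78.5% in each arm at 5% complicated and 77.0% in each at 10%. The expected difference is zero for any *w* and any prognosis.

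**The case against.** The strongest reply is that the objectives are shorthand and other sections fix the groups. Section 4.9.2 forms them by randomisation, so its reference to receiving the device can be read as the assignment. The first note to Table 3 in section 10 describes the randomised allocation itself as being with and without the device, which is almost the phrase used in 3.2.2. Section 6 compares FACT-Cx scores between the groups. For 3.2.2 this largely succeeds, and only a wording alignment is left. For 3.2.3 it does not: the wording there is use of the device, and section 6 offers no analysis sentence to override it.

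A second reply is that analysis sets are normally defined in a statistical analysis plan, which is not at hand. That is right, and their absence is not the complaint. The complaint is that the objective, as worded, sets a grouping at odds with the randomised groups, and a later plan written to match it would inherit that.

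A reader might also infer more than the text supports:
- *That women whose device is withheld are definitely moved to the comparison group.* No section says whether they stay in their arm, are excluded or are regrouped. The regrouping follows only from taking 3.2.3 literally.
- *That the bias must flatter the device.* This needs complicated excisions to have worse visibility at 3 and 6 months. That is plausible, but the protocol does not say so, and the table shows a nil or reversed bias otherwise.
- *That the stenosis comparison is affected too.* Section 6 words that one by group, not by use.

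**Conclusion.** The point holds for 3.2.3. Read with 4.8, its wording gives an as-used comparison that conflicts with the randomised groups of 4.9.2. The bias would probably favour the device if complicated excisions have worse visibility: about 3 to 5.5 percentage points under the assumed 5% to 10% complicated and 80% v 50% visibility. Both the size and the direction rest on inputs the documents do not give. What does not depend on them is that the as-used groups are no longer those that randomisation made. For 3.2.2 the point is only one of consistent wording. As this concerns a secondary objective and a cheap correction, it should be made but does not threaten the primary analysis.

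**What to change.** - Reword 3.2.3 to compare junction visualisation at 3 and 6 months between women randomised to DUDA and women randomised to no device. Reword 3.2.2 in the same way for consistency.
- Add one sentence to section 6: the groups are the randomised arms, whether or not the device was placed or kept. It should cover junction visualisation as well as stenosis and FACT-Cx.
- Keep grouping by actual use for describing device harms and, if wanted, for a supportive analysis labelled as such.

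The cost is a few words in section 3.2 and a sentence in section 6. The statistical price is slight dilution: if a share *w* of the device arm goes without the device and the effect would otherwise be the same in all women, the expected difference is (1 − w) times the full effect, that is 95% of it at 5% withheld and 90% at 10%. The clinical rule in 4.8 and the sample size are unchanged.

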Endocervical canal stenosis (early and late) will be assessed through clinical information and physical examination at each visit to the hospital after surgery. The participant will be asked about menstrual flow and dysmenorrhea during anamnesis, which would indirectly show whether the endocervical canal is patent or not. In the physical examination, after viewing the cervix through specular examination, the doctor will check the permeability of the canal by introducing the hysterometer through the cervical canal. The difficulty of introducing the 2.5mm hysterometer through the channel will be noted according to the following scale:

The possible passage of the hysterometer?

( ) No difficulty

( ) Little / Moderate difficulty, however possible passage of the hysterometer

( ) Could not pass

4.10.3. Quality of life:

Quality of life questionnaires are used in clinical trials and include important outcomes such as postoperative pain and related symptoms. For these assessments, in the present study, the following instruments will be used:

a) Functional Assessment of Cancer Therapy - Cervix Cancer (FACT-Cx), version 4.0, in Portuguese (Annex 1).

b) Universal Pain Assessment Tools: comprises the Visual Analog Pain Scale (VAS), the Numeric Visual Pain Scale (EVN) and the Faces Pain Scale (EF) (Annex 2).

4.11. Study interruption rules:

Below are the study interruption criteria:

a) Registration of a single grade 5 adverse event at any stage of the study;

b) Record of two grade 3 or 4 adverse events in the first stage of the study;

c) Record of two grade 3 or 4 adverse events in the second stage of the study;

d) the benefit of using the device under interim analysis;

e) Identification of considerable risk to participants not provided in this research protocol.

In any of the aforementioned situations, the researcher, before interrupting the study, will communicate the Research Ethics Committee (CEP) of the Barretos Cancer Hospital and await the substantiated opinion, unless the risk to the participants is imminent. In the latter situation, the researcher will interrupt the study to safeguard the research participants and will communicate the CEP as soon as possible.

4.12. Study visits and data collection:

TABLE 1 summarizes the activities carried out in the study according to the time of the visits.

4.12.1. Baseline visit:

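### Objective 3.2.4 describes menstruation only in device users and specifies no between-arm comparison, so the figures have no reference

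*Protocol*

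**What the plan says.** The menstrual aim in section 3.2.4 of the protocol is to "Describe menstrual periods in women who used device placement after surgery". Both the verb and the population differ from the objectives around it. Objective 3.2.2 is to "Compare the quality of life in women with and without the device after surgery", and objective 3.2.3 likewise compares visualisation of the squamocolumnar junction between device and no-device women.

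Section 4.10.2 sets out the data collection: "The participant will be asked about menstrual flow and dysmenorrhea during anamnesis". It does not restrict this by arm. The questions form part of the stenosis assessment, which "will be assessed through clinical information and physical examination at each visit to the hospital after surgery". Table 1 agrees, marking medical history at all six postoperative visits (15 and 30 days; 3, 6, 12 and 18 months).

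The Introduction gives the background: "The complications inherent to conization involve stenosis of the cervical canal, amenorrhea, dysmenorrhea and deep dyspareunia". The second stage has two randomised groups, "one who will receive the DUDA device after CAF and another who will not receive it" (section 4.9.2).

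Section 6 names between-group tests for stenosis rates and FACT-Cx scores. It names no menstrual analysis.

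**The concern.** By the protocol's own account, conization alone can alter menstruation, and every woman in the second stage has conization. A menstrual change seen in device users could come from the excision, from the device, or from both. A table of device users cannot separate these. A high frequency of dysmenorrhea could be read as harm from the device and a low one as benefit, with no support for either reading.

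The trial has a concurrent randomised group that is asked the same questions. The objective as worded does not call on it. Section 2 faults earlier device studies for lacking randomisation, and objective 3.2.4 repeats that limitation inside a randomised trial.

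The population is a second weakness. Women who used the device are defined by what happened in theatre and not by allocation.

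**Working it through.** The protocol gives no menstrual event rate, effect size or precision target, so there is no stated figure to reproduce. The check is first a comparison of the text, then an illustration of what a two-arm table would deliver.

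**Text side by side**

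1. *Population of the objective:* device users only (3.2.4). Objectives 3.2.2 and 3.2.3 cover both groups.
2. *Population asked:* all participants, at each postoperative visit (4.10.2, Table 1).
3. *Exposure to conization:* both arms (4.9.2), with amenorrhea and dysmenorrhea listed as its complications (Introduction).
4. *Analysis:* no menstrual comparison in section 6, so nothing there widens 3.2.4 to both arms.
5. *Users versus allocated:* section 4.8 says the device will not be placed, even after randomisation, if a complication during CAF requires additional procedures. A user-based group therefore leaves out some complicated operations that remain in the no-device arm. The documents do not show which way this would shift menstrual outcomes.

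Items 1 to 4 establish that, as written, the device figures have no reference. Item 5 establishes that comparing users with controls would not be a comparison of randomised groups.

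**Precision of a two-arm table (illustration)**

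Inputs:
- n = 120 per arm, from section 5.2: "this stage of the study will recruit 120 women in each arm, totaling 240 participants".
- Event rate p: not in the documents. Assumed to be 10%, 20% or 30%, and equal in both arms.
- Share menstruating: not in the documents. Section 4.3 admits ages 18 to 65, so it is below 100%. Assumed to be 100%, 80% or 60%.
- No loss to follow-up.

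Half-width of the 95% interval for the difference: 1.96 × √(2p(1 − p)/n).

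All 120 women per arm menstruating:
- p = 0.10: 1.96 × √(0.18/120) = 7.6 points
- p = 0.20: 1.96 × √(0.32/120) = 10.1 points
- p = 0.30: 1.96 × √(0.42/120) = 11.6 points

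At p = 0.20 with fewer menstruating:
- 80%, n = 0.8 × 120 = 96: 1.96 × √(0.32/96) = 11.3 points
- 60%, n = 0.6 × 120 = 72: 1.96 × √(0.32/72) = 13.1 points

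The device arm alone, 1.96 × √(p(1 − p)/120), has half-widths of 5.4, 7.2 and 8.2 points at the three rates. Those intervals are narrower, but they concern a single proportion and say nothing about a difference between arms.

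**The case against.** The strongest reply is that 3.2.4 is descriptive on purpose. It says describe where its neighbours say compare, and it makes no causal claim. The device has a central lumen and stays in the canal until the 30-day visit, so the aim may simply be to record how women menstruate with it in place. The text permits that reading but does not state it. Even on that reading, women in the same 30 days after conization without a device are the natural reference for judging altered flow or pain.

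A second reply is that the contrast is partly made elsewhere. Menstrual history feeds the stenosis assessment, which is compared between groups, and quality of life is compared too. That is fair, but neither comparison reports menstruation directly.

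A third reply is that tabulation belongs in the statistical analysis plan, which is not available here. Methods may well be set there, and it could add a comparison. The objective and its population, however, are fixed in the protocol.

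Two stronger readings are not supported:
- A reader might infer that the control data will be thrown away, or that a comparison is ruled out. The protocol has the data collected in both arms, and nothing in it forbids showing them by arm. It only fails to call for this.
- A reader might infer that menstrual obstruction is the main way stenosis affects the patient. Section 1.1 also names infertility and the loss of early detection of recurrence.

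**Conclusion.** The point stands as a minor one. The protocol asks for a device-only description of an outcome that it says conization itself affects, although it questions both arms. Without the control figures, that description cannot inform whether the device helps, harms or does nothing. The reference to use of the device also departs from the randomised group.

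The gain from a two-arm table is real but limited: an estimated difference with a half-width of roughly 10 points at an assumed 20% rate and 120 per arm, widening to about 11 to 13 points if 80% to 60% menstruate. Both the rate and the menstruating share are assumptions. No error rate or sample-size figure changes, and the primary conclusion is unaffected.

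**What to change.** Reword objective 3.2.4 along these lines: *describe and compare menstrual flow and dysmenorrhea between women allocated to the device and women allocated to no device, in the second stage.* Report both arms at each postoperative visit with the difference and its 95% confidence interval, and label the analysis secondary and exploratory. First-stage women have no control group and can be described separately.

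Restrict the comparison to women who were menstruating before surgery, if the baseline form records this. That cannot be confirmed from the protocol: Table 1 marks medical history only after surgery, and the baseline annex cited in section 4.12.1 is not shown. If the item is absent, add it to the baseline interview.

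The cost is one more table, possibly one baseline question, and a set of intervals over up to six visits without multiplicity adjustment, which the exploratory label should make plain. No extra participants or visits are needed.
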